### Sample size and power

The calculation of the number of subjects needed is based on the effectiveness outcome, on the basis of the following assumptions: risk α equal to 5%, statistical power equal to 80, 5% deprescribing proportion in control group based on current trend, a proportion of at least 15% in the intervention group, an intraclass correlation coefficient of 0.05 (26) and a number of 20 GP-CP pairs per arm. The number of patients to be recruited will be 400 (200 per arm), based on the inclusion of 10 patients per GP-CP pair, with 20 GC-CP pairs per arm during the 12 months of inclusion (27). To reach target sample size, various networks will be involved in recruitment: primary care research network, professional associations, regional unions of practitioners, university training masters.

### Statistical analysis

Variables measured at inclusion will be described according to the randomization group for all included patients. Quantitative variables will be described using the mean, standard deviation, quartiles and range. Qualitative variables will be described using the numbers and proportions for each modality.

In order to measure the impact of the intervention in real life, the analysis will focus on the intention-to-treat population: all patients included will be kept in the analysis sample according to their randomization group, regardless of protocol deviations.

For the effectiveness endpoint, a mixed logistic model will be built to study the proportion of deprescribing between MI condition (intervention) and usual care condition (control), and concomitantly accounting for the cluster effect associated with our design (28). For secondary analysis, the impact of the intervention on quality of life, anxiety disorders, sleep quality, dependence and autonomy will be estimated by comparing the EQ-5D-5L, GAD-7, ISI, ECAB, and IADL scores between the two groups using mixed models. As advocated by the literature (29), models will be adjusted on baseline covariates that are prognostic of the outcome, balanced or not at baseline, including *a minima* the following: age, sex, number of past attempts, suspected addiction. The impact of the intervention on hospitalizations and deprescribing failures will be estimated from hospitalizations (number of hospitalizations) and failures (number of discontinuations and then resumption).

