##### Effectiveness

The effectiveness will be assessed by the cessation or reduction of BZDR use at 12 months from inclusion. It will be described as the proportion of patients no longer being dispensed BZDR at 10 months after inclusion, with the last two months (10 to 12 months) not counted to account for possible residual BZDR use, or having decreased their average Daily Drug Dose (DDD) dispensing by 50%. The decrease will be calculated by comparing the average DDD dispense over the last 3 months of patient follow-up to the dispense observed during the 3 months prior to inclusion.

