#### Aim 2: patient reported outcomes

Secondary outcomes will aim to evaluate improvement in patients reported outcomes, and use of other substances. Patients’ quality of life (measured by EQ5D-5L), anxiety disorders (GAD-7), quality of sleep (ISI), time to first hospitalization after inclusion (SNDS), occurrence of falls, dependence on BZDR (ECAB), autonomy (IADL) and use of other substances will be assessed.

A stratified analysis by type of BZDR (hypnotic or anxiolytic) will be carried out on each of the outcomes to determine the impact of the indication on the implementation elements.

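### The raw stop-then-resume count mixes more stop attempts with more relapse, and hospitalization is listed as time to first event but analysed as a number

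*Protocol article*

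**What the plan says.** All references are to the protocol article.

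- **Failures.** The last sentence of Statistical analysis reads "The impact of the intervention on hospitalizations and deprescribing failures will be estimated from hospitalizations (number of hospitalizations") and, for the second outcome, "failures (number of discontinuations and then resumption"). It gives no denominator and does not tie the figure to the number of patients who stop. Failures are not listed among the outcomes in the Aim 2 section or in Table 3.
- **Hospitalization.** The Aim 2 section lists "time to first hospitalization after inclusion (SNDS"). The sentence above uses the number of hospitalizations instead. No time-to-event method is named anywhere in the article.
- **Effectiveness endpoint.** The Effectiveness section counts a patient as a success if BZDR are no longer dispensed, "or having decreased their average Daily Drug Dose (DDD) dispensing by 50" per cent.
- **Planning figures.** Sample size and power assumes "5% deprescribing proportion in control group based on current trend" and "a proportion of at least 15% in the intervention group", with 200 patients per arm.
- **Population.** The analysis keeps all included patients in their randomized group.

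**The concern.** Resumption presupposes a stop. A control patient who takes the drug unchanged for 12 months can never be a failure; an intervention patient who stops for some months and then restarts is one. The intervention is meant to increase stopping, so if it works it puts more patients at risk of failing. A difference in the raw count could then reflect more relapse among those who stop, more attempts to stop, or both, and the count alone cannot separate them. A reader would probably take an effect on failures to mean an effect on relapse.

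The hospitalization issue is separate. Time to first admission and number of admissions are different outcomes that need different models. They can disagree, for example when a few patients are admitted repeatedly. With one in the outcome list and the other in the analysis, it is open which result answers the question.

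**Working it through.** **1. The plan's own figure.** The sample size reproduces. With 5% versus 15%, two-sided alpha 5% (sidedness is not stated) and 80% power, the unpooled formula gives (1.96 + 0.84)² × (0.05×0.95 + 0.15×0.85) / 0.10² = 137.4 per arm. The design effect is 1 + (10 − 1) × 0.05 = 1.45, and 137.4 × 1.45 = 199.2, against the stated 200. The pooled formula gives 141 × 1.45 = 204.5. The point below does not touch this figure. The article states no expected figure for failures or hospitalizations.

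**2. What drives the failure count.** Let e be the proportion of an arm that ever stops and r the proportion of those who resume, counting at most one failure per patient. Expected failures per 200 are F = 200 × e × r. Hence

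F(int) / F(con) = [e(int) / e(con)] × [r(int) / r(con)].

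With equal r, the second factor is 1 and the ratio of failures is simply the ratio of ever-stoppers.

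**3. Illustration.** The article gives neither e nor r. Suppose that the 5% and 15% were all sustained stops (s). Then e = s / (1 − r) and F = 200 × s × r / (1 − r). The values of r are assumptions.

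| r, both arms | Control failures per 200 | Intervention failures per 200 | Ratio |
|---|---|---|---|
| 20% | 2.5 | 7.5 | 3 |
| 30% | 4.3 | 12.9 | 3 |
| 40% | 6.7 | 20 | 3 |
| 50% | 10 | 30 | 3 |
| 60% | 15 | 45 | 3 |

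The constant ratio is 15/5 restated. It is a consequence of the supposition and not an independent result.

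**4. How far the ratio depends on the supposition.** The 5% and 15% include patients who only reduced. If a share k of the successes in each arm are sustained stops, the ratio at equal r is 3 × k(int) / k(con). It stays at 3 if the shares are equal. It falls to 3 × 0.5 = 1.5 if the intervention share is half the control share, and to 1 if it is one third. It rises above 3 if the intervention share is the larger. The article gives neither share.

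**5. When the direction changes.** Still reading 5% and 15% as sustained stops, the counts are equal when r(int)/(1 − r(int)) = (5/15) × r(con)/(1 − r(con)).

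| Control r | Intervention r at which counts are equal |
|---|---|
| 20% | 7.7% |
| 40% | 18.2% |
| 50% | 25% |
| 60% | 33.3% |

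With 30% against 50% in control, the intervention count is still higher (12.9 versus 10) although its relapse risk is lower. With 30% against 60%, it is lower (12.9 versus 15).

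**6. Hospitalization.** No arithmetic applies. The Aim 2 section lists a time to a first event; the Statistical analysis section lists a number of events; no sentence links the two or says which one is reported as the secondary outcome.

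**The case against.** Five points can fairly be made on the other side.

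- **The article names the data, not a model.** It gives no effect measure for failures, and a full protocol or analysis plan may add a denominator. This limits confidence. It does not clear the text, which fixes a number of events as the basis for the intervention's impact and contains nothing that corrects it.
- **A count over all included patients is a valid randomized comparison.** This stands. It estimates the total effect on stop-then-resume events without selection. The fault lies in what it is taken to measure: it is misleading as a measure of relapse.
- **It would be read beside the effectiveness endpoint.** That helps, but the endpoint merges stopping with halving the dose, so it does not show how many patients were at risk of resuming.
- **The size is assumed.** This stands. A reader might infer from the illustration that the trial will report three times as many failures, or that the intervention will appear harmful. The documents support neither. At r = 30%, even the illustrated difference, 4.3 versus 12.9 per 200, gives z = 0.0429 / √[(0.0214×0.9786 + 0.0643×0.9357) / (200/1.45)] ≈ 1.8, short of two-sided 5% significance; higher assumed r would pass.
- **The two hospitalization measures can coexist.** Both can come from the SNDS, hospitalizations are also collected for the cost-utility analysis, and the Statistical analysis section is not exhaustive: falls and use of other substances are also absent from it. So a reader should not infer that the time-to-event outcome was dropped, or that the Aim 2 wording is the intended one. What remains is that the two sections name different measures for one outcome without ranking them.

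**Conclusion.** The point holds in two limited parts.

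First, the raw count does not isolate relapse. At equal resumption risk it rises in proportion to the number of patients who stop, so success in producing stops appears as more failures. That relation is exact under the simplification of one failure per patient. Its size in this trial is unknown, and its direction is likely only if the intervention does not lower resumption enough to offset the extra stops. The ratio of 3 rests on reading the 5% and 15% as sustained stops, which the endpoint definition does not support.

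Second, the hospitalization outcome is stated in two incompatible ways. The documents do not show which is intended.

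Both parts concern secondary analyses and should be settled before analysis. Neither affects the effectiveness endpoint, its mixed logistic model or the sample size.

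**What to change.** **Failures.** State that the raw count will not be read as the effect on relapse. Compare between arms, over all included patients and with the cluster effect, an M12 status with four levels:

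1. neither a stop nor a 50% reduction;
2. reduced by at least 50% without stopping;
3. stopped and resumed;
4. stopped and sustained.

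The separate level for reducers is needed because they are successes under the effectiveness endpoint and would otherwise be filed with patients who changed nothing. A simpler alternative is sustained cessation alone as the between-arm contrast. Report resumption among stoppers descriptively, with the number of stoppers as denominator. Stoppers are selected after randomization, so that figure should not be presented as a causal comparison.

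**Hospitalization.** Reconcile the two sections. Name one measure as the secondary outcome with a matching cluster-adjusted analysis (a time-to-event model if the Aim 2 definition is kept, a count model if the number is kept), and label the other supportive.

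**Cost.** A few lines of wording in the protocol or analysis plan before analysis. The SNDS dispensing and hospitalization data already planned are sufficient; no new data or patients are needed.

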## Discussion

The objective of this trial is to assess the added value of a primary care collaboration between GPs and CPs in order to implement inappropriate BZDR deprescribing in older adults. In various countries, legislative and regulatory developments have led to an expansion of the scope of practice of pharmacists for the substitution or discontinuation of certain medications, including BZDR (30). The patient-centered intervention developed in this study aims to reinforce known levers and overcome barriers to stopping inappropriate medications.

Wei et al., in a 2022 meta-review, reported that improving interprofessional collaboration requires organizational, teams, and individuals’ combined efforts but that when effective collaborations occur, all stakeholders can benefit – organizations, professionals, and patients. Our study is grounded in a concrete way on existing collaborations. It strengthens the bond between physicians and pharmacists who work together on a daily basis. This pragmatism is a major implementation tool when setting up studies in primary care.

The use of MI techniques have demonstrated their effectiveness in various studies (31, 32) and allows us to hypothesize that this intervention will be beneficial to a patient who is initially reluctant to stop or reduce his or her consumption of BZDR. Indeed, the literature suggests that MI is a powerful tool for BZDR deprescribing, as it is popular with healthcare professionals (33) and has been shown to be effective with other drugs such as opioids (34). A recently published review (35) described that different interventions had a positive impact as soon as they were based on patient empowerment (36–38). MI, for this purpose, is based on taking into account the ambivalence a patient may have about taking action. This ambivalence is well described: patients are aware of the benefits of stopping their BZDR (perception of long-term side effects, burden of treatment, desire for natural sleep), but face inner barriers that block initiation or persistence of cessation (fear of withdrawal effects or return of pathology) (39). Perceived self-efficacy, which may be due to a previous failure to quit, or a lack of knowledge about how to cut down, may also come into play (40). All of these factors provide fertile ground for the implementation of MI in the deprescription of BZDRs in our study. The expected results are a decrease in BZDR consumption for patients in the intervention arm compared to the control group. In addition, this study could show an improvement in cognitive functions (41–43), an improvement in the quality of life of patients (32, 44, 45) and an economic benefit of the deprescribing intervention. Training pharmacists in MI through a specific two-day hands-on training should improve the adoption of the intervention by health professionals. Moreover, as this technique can also be used on other occasions (smoking cessation, therapeutic adherence, etc.), we believe that it is a lever for the involvement of pharmacists in the trial and for the development of a more effective approach. In addition, accompanying CPs during the first interviews should be important levers for the implementation of the MI.

Patient empowerment is a key mechanism for increasing responsibility for shared decision-making with health care providers (46). It is an effective strategy when it comes to deprescribing (47) combined with behavior change strategies and progressive de-escalation. Patient empowerment, in which patients strengthen their ability to effectively care for themselves, has been shown to be a powerful transformative process (31), and giving them educational material may promote deprescribing conversations (48). Combined with direct education, these methods have been shown to be effective in reducing inappropriate use of BZDR in the older adults (49). This tripartite approach for pharmacists, physicians and patients aims to achieve a synergistic impact.

### Strengths

Strengths of the study include its pragmatic design that will allow the observed process to reflect real-world practice as accurately as possible. This pragmatic approach involves intervention at the group level, rather than the individual level, and as such cluster randomizations are the most common (50). Furthermore, this cluster-randomized design is considered the most appropriate for conducting deprescribing trials (51). To our knowledge, this is the first deprescribing trial in France involving interprofessional collaboration of GPs and pharmacists in primary care. Multiple implementation outcomes will allow us to assess how this intervention can be scaled up beyond the clinical trial. Indeed, the qualitative study will allow us to explore the appropriateness of the program by assessing the experiences and representations of the pairs and patients concerning deprescribing. This part will highlight the obstacles and levers to intervention. Finally, an objective assessment of BZDR discontinuation rates from the National Health Insurance database will increase the internal validity of the study.

### Limits

Despite these strengths, our trial has several limitations. Firstly, neither the patients nor the GP-CP pairs will be blinded due to the pragmatic design of the trial (52). However, the statisticians and the clinical research officer will be blinded to reduce the risk of confirmation, monitoring and evaluation bias. Secondly, it is likely that the pairs agreeing to participate in the study will be health professionals already convinced by the deprescribing approach, which is why this study is randomized and controlled. In addition, although pharmacists will be trained in MI by a certified organization, some may be more or less comfortable than others and the implementation of the intervention may depend on the operator of the training. This will be measured by the fidelity of the study to the protocol. Finally, a limitation of this study is that the evaluation of a multifaceted intervention prevents the determination of the specific component(s) responsible for the observed outcomes or failures at the conclusion of the study.

## Conclusion

This study will provide evidence on the effectiveness of a joint GP-CP intervention to aid benzodiazepine deprescribing. If so, this strategy and intervention could be implemented more widely and also for other potentially inappropriate drugs in older people.

## Ethics statement

Ethics committee (CPP Nord Ouest 1) reviewed and approved the study protocol on December 1st, 2022 (22.03226.000131).

## Abbreviations

BZDR: Benzodiazepines and related drugs
CUA: Cost-utility analysis
CP: Community pharmacist
DDD: Daily drug dose
GP: General practitioner
HAS: Health high authority
MI: Motivational interview
QALY: Quality adjusted life year
SNDS: National health data system
